## Introduction

The persistent development and spread of resistance to antimicrobials, especially antibiotics, remain an important public health concern in the UK^1^ and globally.^2 3^ Antimicrobial resistance (AMR) is a major threat to the treatment and control of infectious diseases as drug-resistant infections are characterised by prolonged morbidity, increased risk of disabilities, death and cost of healthcare.^4^ A 2014 review estimated that consistent increases in AMR would lead to about 10 million deaths per year by 2050.^5^ Inappropriate prescribing and use of antibiotics in healthcare practices, especially primary care, are integral to the development and spread of resistance.^6 7^

About 74% of the antibiotics prescribed in England in 2016 was in primary care.^8^ The high rate of antibiotic prescribing in primary care has been associated with increased AMR.^9^ While some of the antibiotics prescribed in primary care settings are appropriate, a substantial proportion are cases where antibiotics are not clinically indicated, such as suspected respiratory tract conditions, which can be self-limiting.^9 10^ Uncertainties about diagnosis, (perceived) patient expectations for antibiotics, occupational pressure (eg, consultation rate) and previous experiences are some of the identified drivers of overprescribing in primary care practices.^11–16^

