### Data sources

The study will constitute secondary analyses of antibiotic prescribing data from NHS England covering the period 2013 to 2018. CCGs were established in England in April 2013 following the Health and Social Care Act 2012.^33^ Data on antibiotic prescribing in primary care at CCG level will be sourced from the NHS England Antibiotic Quality Premium Monitoring Dashboard, which is produced by the NHS Business Services Authority (BSA).^34^ Primary Care prescribing data are publicly available from the NHS BSA website. The dataset contains the number of antibiotic items (STAR-PU) prescribed in each CCG from the financial year 2015/2016 to 2018/2019, with data for October 2018 the latest at the time of this protocol. Data for the period 2013 to 2015 will be mapped to CCG level from the practice-level data.

Practice-level antibiotic prescribing data will be sourced from OpenPrescribing, an Evidence-Based Medicine DataLab project by the University of Oxford. OpenPrescribing publishes monthly antibiotics prescribing data from August 2013, with data for October 2018 the latest at the time of this protocol. Practice-level antibiotic prescribing data from OpenPrescribing is not STAR-PU weighted, so the extracted data will be STAR-PU weighted using figures from the 2013 Item-based age–sex weighting for oral antibacterials^14^ and the number of registered patients in each age–gender category in a practice for each specific month.

Overall, the dataset offers coverage of at least 3 years postintervention given that antibiotic prescribing became a QP priority in March 2015. This will be important in investigating the immediate direct and indirect effects of the QP initiative while giving an insight into the sustainability of the identified effects (if any) in the long-term.

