### Variables

The predictor will be a binary variable indicating the implementation of the QP intervention. The intervention will include all periods after March 2015 when the 2015/2016 QP guidance in England was published, while the control will be periods prior to this. The primary outcome of interest is the rates of antibiotic prescribing at CCG level in England, which will be a continuous variable indicating the number of items (per STAR-PU) prescribed per month.

To account for differences in practice and CCG characteristics that can contribute to variance in antibiotic prescribing, we will be adjusting for the number of general practitioners in each practice (from the NHS Workforce data),^35^ the index of multiple deprivation (from the Department for Communities and Local Government),^36^ prevalence of comorbidities (asthma, chronic obstructive pulmonary disease, diabetes, cancer, chronic kidney disease (from the NHS Quality and Outcomes Framework database)),^37^ the prescribing rate of other non-antibiotic drugs (opioids and benzodiazepines) and seasonal influenza vaccination rate (from PHE).^38^

Mediator variables will be derived from the questionnaire data from a PHE survey,^39^ with 187 of the 209 AMS leads representing CCGs in England and data from other organisations that have evaluated the interventions treated as potential mediators in this study. In the PHE survey, participants were required to complete questionnaire items, which included their adoption of national and local strategies in their respective CCG to enable them to meet QP targets on antibiotic prescribing in primary care. The mediator variables will be binary or continuous variables, indicating the adoption of key interventions and intermediaries that are hypothesised to reflect in the integration of the QP guidance in improving antibiotic prescribing in primary care practices.

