### Handling missing data

Over the period covered by this study (2013–2018), there have been changes in the number of practices and CCGs in England. Some practices have closed, new practices opened and some CCGs merged over the period; as such, we will have missing values for some observations. To maximise the use of existing observations, we will retain all observed values in the main analysis and impute the missing values using multiple approaches.^40^ Missing values for the period before a new CCG was formed through merger of pre-existing CCGs will be imputed using the mean value of the CCGs that constitutes the merger; subsequently, these closed CCGs will be dropped from the dataset. Other missing values in this study will be handled using multiple imputation method on Mplus V.8.2. We will run a separate imputation model for the practice and CCG level datasets, the results will be averaged across 20 imputed datasets. Complete case analysis will be conducted as part of the sensitivity analyses for this study to examine the consistency of the results from the imputed set.

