## Limitations

This study has some limitations. The survey that provided data on mediator variables included 187 of the 209 CCGs existing at the time of the study. However, this sample size is large enough for strong statistical power, and multiple imputation will be used to address issues on missingness. Furthermore, due to the limited data on practice-level interventions or strategies that might potentially mediate the effect of the QP on antibiotic prescribing, we will not be able to extensively investigate the mechanism of QP impact at the practice level. Nevertheless, extensive investigations will be conducted at CCG level where we have more data on potential mediators.

In 2013, the Primary Care Trusts in England, which were responsible for planning and commissioning healthcare services at the primary care level, were transformed to CCGs.^50^ As such, our investigations are restricted to the CCG era. This is important as the QP initiative is implemented and rewards paid out at CCG level.

We recognise that the causal interpretation of any effect from our mediation analysis rests on assumptions such as sequential ignorability and exchangeability. Causal inference from this analysis will be limited given that our data are observational with the absence of random assignment of cases to treatment and mediator levels, as well as the likelihood of unmeasured confounders. The rate of consultation for conditions where antibiotics might be prescribed is one of the unmeasured confounders in our study. This has not been accounted for in our analyses as these data are not available nationally at the practice level.

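### GP supply is adjusted for as a headcount per practice, which mainly reflects practice size; GPs per registered patient would fit the purpose better, and the denominator is already held

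*Protocol article*

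**What the plan says.** The Variables section gives the purpose of adjustment: "To account for differences in practice and CCG characteristics that can contribute to variance in antibiotic prescribing". For GP supply, "we will be adjusting for the number of general practitioners in each practice (from the NHS Workforce data". No denominator is given. Three other covariates in the same list (comorbidity, prescribing of other drugs, influenza vaccination) are written as prevalences or rates, and the outcome is scaled to population: "The primary outcome of interest is the rates of antibiotic prescribing at CCG level in England", in items per STAR-PU per month.

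Four other places bear on this:

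- The Introduction states that "occupational pressure (eg, consultation rate) and previous experiences are some of the identified drivers of overprescribing in primary care practices".
- The Limitations section concedes: "The rate of consultation for conditions where antibiotics might be prescribed is one of the unmeasured confounders in our study".
- Handling missing data reports that "Some practices have closed, new practices opened and some CCGs merged over the period". It fills the period before a merged CCG existed with the mean of the CCGs that formed it.
- Data sources shows that STAR-PU weighting uses item weights "and the number of registered patients in each" age and gender group, by practice and month. List size per practice is therefore already in hand.

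The covariates enter the mediation models, which compare the financial year before QP with one later year (Statistical analysis). The interrupted time series is univariate and contains none of them.

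**The concern.** A headcount answers a different question from the one the Introduction raises. Pressure on prescribers depends on how many patients each GP serves, and two practices with identical staffing per patient can differ twofold in headcount. The adjustment therefore controls for size and largely leaves GP supply uncontrolled.

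The second issue is time. In the mediation models the exposure is calendar period, so any covariate whose average changes between the compared years is correlated with exposure. If practices close and their GPs and patients move to those remaining, mean GPs per practice rises with no change in staffing per patient. At CCG level, where the primary outcome sits, a total avoids that drift but tracks population and is exposed to the rule for merged CCGs. Part of a before/after difference could then be assigned to, or taken from, the GP covariate for reasons unrelated to staffing.

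**Working it through.** The protocol gives no figure for this point, so there is none to reproduce. Inputs not in the protocol are marked as assumed.

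**1. Headcount against supply.** Take 8 GPs for 14,000 patients and 4 GPs for 7,000 (illustrative). Supply is 8/14 = 0.57 and 4/7 = 0.57 GPs per 1,000, which is identical. The covariate as written takes the values 8 and 4.

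**2. Drift of a mean per practice.** With GPs and patients fixed and a share m of practices lost, mean GPs goes from 5 to 5/(1 - m). The shift in the QP coefficient is approximately the slope of rate on GP count times the change in mean count. Assumed: 5 GPs per practice, m of 5-10%, slope 0.5-2% of the mean rate per GP.

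| m | Mean GPs | Change | Shift at 0.5% | Shift at 2% |
|---|---|---|---|---|
| 5% | 5.26 | 0.26 | 0.13% | 0.53% |
| 10% | 5.56 | 0.56 | 0.28% | 1.11% |

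The range is about 0.1-1.1% of the mean rate. For scale, the Introduction gives QP reduction targets of 1% (2015/2016) and 4% (2016/2017). With a zero slope or no change in mean count, the shift is zero. GPs per 1,000 does not move here, but only because GPs and patients were held fixed by assumption.

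**3. Simulation check.** Assumed: 7,000 practices; median list 7,000; on average 0.65 GPs per 1,000 (about 5.2 per practice); rate falling by 20% of the mean per additional GP per 1,000; true QP effect -4.0% of the mean rate; a fixed practice trait related to size; 5, 10 or 15% of practices lost by combining with another.

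| Size-prescribing slope per GP | QP estimate adjusted for headcount (5/10/15% lost) |
|---|---|
| -1% | -3.75 / -3.45 / -3.14% |
| 0 | -3.95 / -3.92 / -3.87% |
| +1% | -4.14 / -4.30 / -4.47% |

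Adjusted for GPs per 1,000, the estimate stayed between -3.91% and -4.07% throughout. With no practices lost, both covariates gave about -4.0%. Headcount correlated about 0.93 with list size and about 0.3 with GPs per 1,000. These correlations follow from the assumed distributions.

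**4. CCG total at a CCG merger.** Let two CCGs have A and B GPs. The fill rule, if applied to a total, gives the merged CCG (A + B)/2 before the merger, while the observed value afterwards is A + B. The covariate doubles with no change in staffing. For a ratio, the mean of the two constituent ratios differs from the pooled value only by weighting, and pooling GPs and lists before dividing removes that difference too.

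**The case against.** The strongest reply is that the protocol never calls this covariate a measure of workload. It lists it among practice and CCG characteristics, and practice size is a legitimate one. The article is also condensed, so scaling and aggregation to CCG level may be set out elsewhere. Both points have weight, but the covariate named is a count per practice, and size can be entered more directly as list size.

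Several stronger readings are tempting, and the documents do not support them:

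- *That practice mergers inflate the count.* The article reports practice closures, practice openings and CCG mergers. Practice mergers are an inference. Closures with GPs moving elsewhere would act the same way, but openings could push the mean down.
- *That the covariate absorbs part of the QP effect.* This needs a count updated over time (not stated), a net drift in its mean and a relation between size and prescribing. The shift can inflate the effect as easily as shrink it. If size truly causes lower prescribing, removing the effect of consolidation is correct control, not an artefact.
- *That practice closures distort a CCG total.* If GPs stay within the CCG, the total is unchanged. Only a mean per practice drifts.
- *That workload confounding could be removed with data in hand.* GPs per patient is a proxy, and the Limitations section already discloses that consultation rate is missing. Stable workload differences between practices also do not by themselves confound a before/after contrast.

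**Conclusion.** The point holds as a weakness in how one covariate is defined, not as a demonstrated bias. A headcount per practice mainly reflects size and is a poor stand-in for GP supply relative to patients, whether or not practice numbers changed. Its possible effect on the QP estimate is confined to the adjusted mediation models. It runs through drift in a mean per practice or, if the pre-merger mean rule is applied to a GP total, through an artificial step at a CCG merger.

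The direction is open and the protocol does not allow the size to be fixed. The 0.1-1.1% range rests wholly on assumed GP numbers, practice losses and slopes, and its upper end combines the two least favourable values. It shows that the shift could matter beside a 1% target, not that it will. The change is worth making because it is nearly free.

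**What to change.** - Define the covariate as GPs (full-time equivalent where the workforce data allow) per 1,000 registered patients.
- At CCG level, compute it as total GPs over total list. For merged CCGs, pool the constituents' GPs and lists in the pre-merger period before dividing, and do not average them.
- If practice size is wanted as an adjustment, enter list size as a separate covariate.
- State that the ratio is a partial proxy for workload and that consultation rate remains unmeasured.

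The cost is minor extra data handling, with list sizes already obtained for STAR-PU weighting, and one more covariate if list size is added.

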### Statistical analysis

Our first analysis will be an interrupted time series to investigate whether antibiotic prescribing rate in England has changed over time, and how such changes, if any, are associated with the QP implementation in March 2015. This will be conducted using the ordinary least square regression method^41^ to assess whether the 2015/2016 QP establishment resulted in a shift in the level and trend in antibiotic prescribing in primary care in England compared with the period before the intervention. Using the practice-level dataset, a univariate time series with the mean antibiotic items (STAR-PU weighted) prescribed in all primary care practices in England for each month will be conducted using the *ITSA* function on Stata, with post-trend specification to show a postintervention trend. The Cumby-Huizinga general test for autocorrelation will be used for general specification test of serial correlation in the time series data.^42^

A new QP guideline was implemented each financial year with changes in the prescribing rate target and the proportion that improved prescribing constituted in the QP award for each year. Our mediation analyses will investigate the effects of the QP by comparing antibiotic prescribing rate in the financial year before its implementation to each subsequent year postimplementation; as such, our dataset for the mediation analyses will have the control group as the financial year before QP and the intervention group as a specific post-QP implementation year. Three analyses will be conducted for each of the three financial years since QP establishment. This will enable us to compare the effects of the different target levels that have been set over the years and the proportions of the QP award attributed to improvement in antibiotic prescribing.

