Using a unified model for the natural direct and indirect effects,^31^ we will investigate the relationship between the QP initiative, the potential mediators and antibiotic prescribing rate with adjustment for the practice and CCG characteristics. This approach addresses the issues associated with the traditional approach to mediation analysis that obtains natural direct and indirect effect estimates through a non-trivial combination of parameter estimates from multiple models for the regression of the mediator and that of the outcome.^32 43^ Also, the unified model is applicable to nonlinear regressions, different measurement types for outcome and mediator variables, and allows for interaction between the exposure and the mediator.^31^

We will first fit single-mediator models with each mediator separately modelled using the *medeff* function in Stata.^44^ With the single-mediator models, we will be able to establish the individual influence of each potential-mediator variable. Variables that showed a mediating effect in the single-mediator models will be added to build a multiple-mediator model using a sequential mediation analysis method.^45^

A sequential multiple-mediator analysis is preferred to merely summing the effects of the single mediators because the sum may differ from the joint mediated effect, particularly as our potential mediators may influence one another.^45^ Modelling all the significant mediators together provides a more accurate assessment of the mediation effects and causal relationship,^46 47^ while assessing the indirect effect of a group of mediators in explaining how and why the intervention impacts on the outcome. The ordering of the mediators in the sequential mediation analysis will be based on evidence from the literature and the outcome of our stakeholders’ workshop designed to identify possible pathways between the predictor, mediators and outcome. The workshop that will validate our conceptual model will also enable us to identify what mediators affect one another and inform interactions to include in our model. All analysis will be conducted in the Stata statistical package V.15.1.

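### The interrupted time series has no comparison series, so a general break in prescribing around March 2015 cannot be told from a QP effect; the opioid and benzodiazepine rates already planned could serve as a negative-control check

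*Protocol article*

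**What the plan says.** Three choices in the protocol article bear on this point.

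- **Comparator.** Under Variables, the intervention period is everything after March 2015, "while the control will be periods prior to this". The QP guidance applied to all CCGs at once, so there is no concurrent untreated group.
- **Time series model.** Under Statistical analysis, the first analysis is an ordinary least squares interrupted time series, specified as "a univariate time series with the mean antibiotic items (STAR-PU weighted) prescribed in all primary care practices in England for each month". Its purpose is "to assess whether the 2015/2016 QP establishment resulted in a shift in the level and trend in antibiotic prescribing", judged "compared with the period before the intervention". No covariate or second series is named.
- **Role of the other drugs.** Under Variables, the adjustment list includes "the prescribing rate of other non-antibiotic drugs (opioids and benzodiazepines"), and the stated purpose of that list is "To account for differences in practice and CCG characteristics that can contribute to variance in antibiotic prescribing". Adjustment is then described for the mediation models, which relate the QP initiative, "the potential mediators and antibiotic prescribing rate with adjustment for the practice and CCG characteristics".

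The further analyses are complete cases (Handling missing data), implementation dates moved by 1 to 3 months, a binary target-achieved outcome, and subgroups by prescribing level and deprivation (Sensitivity analyses). None uses an outcome that QP should leave unchanged. Limitations qualifies the causal reading of the mediation analysis and names consultation rate as an unmeasured confounder. It does not mention that the time series lacks a control series.

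**The concern.** A segmented regression on one series estimates how far the series departs from its projected earlier trend. It cannot say why. Anything that altered primary care prescribing generally at about the same date enters the level-change or slope-change coefficient with the same weight as QP. Examples are a change in general prescribing policy, in data capture, or in the mix of practices contributing to the national mean. Moving the date by up to 3 months does not help, because it refits the same single series.

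The plan already includes two drug groups that the antibiotic QP does not target. As covariates in the mediation models they do nothing for the time series. Run as outcomes in the same segmented model, they would show whether a break of similar timing and size appears where QP gives no reason to expect one.

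At stake is the attribution of the time series result to QP. The targets set out in the Introduction are small (1% in 2015/2016, then 4% in 2016/2017, of 1.61 items per STAR-PU), so a modest general shift could be comparable in size.

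**Working it through.** The protocol gives no power, alpha or variance figure for the time series, so there is no stated figure to reproduce. The calculations below show how the planned model behaves. They are not evidence about what happened in 2015.

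**Inputs from the protocol article**
- Practice-level data run from August 2013 to October 2018 (Data sources). With the intervention period starting after March 2015, that is 20 months before (August 2013 to March 2015) and 43 after (April 2015 to October 2018), 63 in all.
- Model: level and trend change by ordinary least squares (Statistical analysis).

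**Assumptions not in the document**
- Pre-QP rate scaled to 1, independent monthly noise with SD 2%, two-sided 5% tests.
- In the comparisons with a control, the control drug series shares the common change exactly.
- True QP effect is zero.

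**Step 1. What the single series reports.** Model: y(t) = a + b·t + c·D + d·D·(t - 20), with t = 0 to 62 and D = 1 from t = 20. Means over 2,000 simulations:

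| Common change in all prescribing | Planned single series | Antibiotic minus control series |
|---|---|---|
| 4% fall from April 2015 | level -4.0%, p<0.05 in 94% | level 0.06%, p<0.05 in 4.5% |
| Slope change of -0.10% per month after March 2015 | slope change -0.10% per month | about 0 |
| Steady decline of 0.2% per month throughout | level 0.0%, slope change about 0 | about 0 |

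A general break passes in full into the coefficient read as QP. A steady linear trend that predates March 2015 does not, because the model already removes it. The difference series is shown only to isolate the mechanism; it relies on the control moving exactly with antibiotics, which real series need not do.

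**Step 2. What a negative-control run could detect.** For two separately fitted line segments, the variance of the level change at t = 20 is the sum of two prediction variances, each 1/m + (x - x̄)²/Sxx with Sxx = m(m² - 1)/12:
- Before: m = 20, predicted at 20, x̄ = 9.5, Sxx = 665: 1/20 + 10.5²/665 = 0.2158.
- After: m = 43, predicted at its first month, x̄ = 21, Sxx = 6,622: 1/43 + 21²/6,622 = 0.0899.
- Sum 0.3056, square root 0.553.

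The standard error is 0.553 × 2% = 1.1% (0.55% if the noise SD is 1%). With 59 degrees of freedom (critical t = 2.00), the 95% confidence interval is about ±2.2% (±1.1%). Power from the noncentral t distribution:

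| Shift in the control series | Noise SD 2% | Noise SD 1% |
|---|---|---|
| 1% | 14% | 43% |
| 4% | 94% | above 99% |

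The check can expose a large general break. It says little about one the size of the first-year target.

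**Step 3. Whether the mediation models inherit the problem.** They compare the year before QP with one later year and adjust for these drug rates. A simulation of 209 CCGs over two years (assumed between-CCG SD 12%, common 4% fall, zero QP effect) left an apparent effect of -4.0%, -2.8%, -1.6% and -0.5% when the between-CCG correlation of the two drug rates was 0, 0.3, 0.6 and 0.9. Adjustment removes an unknown part of a general shift, so the result in step 1 does not carry over unchanged.

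**The case against.** The strongest reply is that a single-group interrupted time series is a recognised design for a policy applied everywhere at once, that the Introduction justifies the natural experiment, and that this asks for an extra robustness analysis rather than correcting an error. That is fair as to weight. However, the article itself fixes the univariate model, assigns the other drugs their role and lists the sensitivity analyses, so the choice is open to comment.

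Parts of the reply stand:

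- **Some threats are partly handled.** STAR-PU weighting uses registered patients for each month, and missing values from practice openings and closures are imputed, with a complete-case check. The document gives no sign of an actual break in general prescribing in 2015.
- **The causal language is mixed.** Statistical analysis also speaks of association, and Limitations says causal inference will be limited, though it says so of the mediation analysis.
- **The check is weak for small shifts**, as step 2 shows.
- **It misses antibiotic-specific events**, such as the Chief Medical Officer's letter first sent in September 2014 (Introduction).
- **The control drugs have their own trends.** A break in them need not share a cause with antibiotics.

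Two stronger readings are tempting. A reader might infer that the time series fixes a total effect which the mediation analyses then divide, so that a general shift would invalidate the direct and indirect effects too. The document does not support this: no time-series coefficient is carried forward, and the mediation models have their own year-against-year datasets, total effect and adjustment. A reader might also infer that every general trend is reported as a QP effect. That is wrong for a steady trend already present before March 2015.

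**Conclusion.** The point holds, confined to the interrupted time series. As specified, that analysis cannot distinguish a QP effect from a general change in the level or slope of primary care prescribing that departs from the pre-QP trend around March 2015. No planned sensitivity analysis addresses this, and Limitations does not acknowledge it. In the time series the bias equals the general shift, whatever its size. No figure for that shift can be drawn from the document, so the 4% case is an illustration resting on assumed independent noise and an exactly shared change. This is a design weakness that can be reduced cheaply, not a numerical error or a fatal flaw.

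**What to change.** In Statistical analysis, add the following to the interrupted time series:

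1. Fit the same segmented model, with the same dates, to monthly opioid and benzodiazepine items per registered patient as negative-control outcomes.
2. Justify briefly why the antibiotic QP should not affect these drugs, and note any policies or trends of their own.
3. Report their level and trend changes with confidence intervals beside those for antibiotics.
4. State in advance how the results will be read. A break of similar timing and size weakens attribution of the antibiotic change to QP, without ruling it out automatically. A null result does not prove attribution, because small shifts would be poorly detected and antibiotic-specific events such as the September 2014 letter are not covered.
5. Add a sentence to Limitations that the time series has no concurrent control.

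The drug rates can stay as covariates in the mediation models.

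The cost is two further model runs, plus monthly extraction of the opioid and benzodiazepine data if these were planned only at a coarser interval (the article does not give one). Because these series have their own trends, they should serve as a falsification check and not be subtracted from the antibiotic series.
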